#### Sustainment

6.Increase demand [49] and Access new funding [49]. The evaluation team will develop quarterly reports and share them with VISN leadership in Texas, VA national leadership, local and state leadership, CICs in Texas, and potential CICs in other states. Within the reports, the team will highlight the status regarding VSI implementation and effectiveness variables. Following implementation, the evaluators will report on the overall budget impact analysis to support sustainment at the city level, as well as identify necessary resources to support initiative spread to other states. As part of the budget impact analysis, the evaluators will collect implementation and intervention cost data, including VA and non-VA materials, training costs, dashboard development/technology costs, CIC and transition coordinator personnel time and costs, and travel expenses. VHA healthcare utilization costs will be determined from accessing VHA administrative data on VHA cost and utilization to estimate the budget impact of implementing the VSI program using recommended approaches for budget impact analysis [63]. These health care costs will include VHA inpatient, outpatient, pharmacy, and VHA-paid community care costs with total costs estimated per TSMV per year and adjusted for inflation [17]. This will help to ensure sustainment in Texas and justify further allocation of funding for expansion into other states.

### RE-AIM

The RE-AIM framework (see Table 2, Online supplement) will allow the VSI to plan, assess, and adapt to the complexities resulting from a multi-organizational, collaborative endeavor across numerous locations. City-level analyses will examine RE-AIM measures before, during, and after implementation and facilitate formative and summative evaluation. *Reach* will be assessed by calculating the percent of eligible TSMVs who sign up for the VSI on respective military installations. *Effectiveness* will be assessed by TSMV-level data for proximal and distal variables (See Measures for more information). *Adoption* will be assessed by calculating the percent of sponsor candidates who complete certification and by counting the number of CICs who sign a VA Memorandum of Agreement.

*Implementation* will be assessed by four dimensions [5]: (a) *Fidelity* refers to adherence or program integrity and is the extent to which specified program components are delivered as prescribed [18]. To assess fidelity, we developed fidelity trackers that will assess to what extent core elements of the intervention are delivered as intended (see Table 2, Online Supplement); (b) *Quality of delivery* addresses the skill and behaviors with which sponsors deliver the VSI during their interactions with TSMVs. As part of the evaluation, TSMVs will complete an evaluation of their sponsor through the Leader-Behavior-Description-Questionnaire--Form XII [62] to assess the degree to which they perceive sponsors as engaging in relational-oriented and task-oriented leadership behaviors; (c) *Adaptation* concerns changes made to a program during implementation. Research attests to the value of allowing local communities to adapt programs according to the needs of a local population [47]. Adaptations will be documented and tracked using qualitative data from periodic reflections (see below). For this evaluation, we will (1) determine if observed changes stem from lack of fidelity or adaptation, and (2) categorize adaptations as either additions (i.e., activities or materials not part of the original initiative) or modification (i.e., activities or materials that were part of the original initiative but implemented in a way beyond prescribed variations). Evaluators will recommend sustainment and expansion of adaptations perceived as being effective and beneficial to TSMVs; (d) *Participant responsiveness* is identified as “levels of participation and enthusiasm” ([16], p. 45). We will measure participant responsiveness by calculating the number of sessions TSMV-sponsor pairs attend, percent of initial “My Action Plans” completed by TSMV-sponsor pairs within 30 days of matching, number of monthly updates made to action plans, and level of TSMV satisfaction with the VSI.

*Maintenance* will be assessed after the implementation phase and operationalized as the number of sponsors and CICs that remain engaged with the VSI, number of new sponsors registered, number of newly enrolled TSMVs, and continued VA funding dedicated to sustainment and expansion of the VSI.

### Measures

To facilitate evaluation of the VSI effectiveness, TSMVs will complete a range of online self-report measures and clinical interviews (Table 1; Fig. 2, Online Supplement). TSMVs will provide data at Time 1 (Baseline: 6 months prior to military discharge), Time 2 (2 months prior to military discharge), Time 3 (2 months post military discharge), and Time 4 (6 months post military discharge). To maximize clinical utility of data, many included measures are routinely administered at VA medical centers.

**Table 1 Tab1:** Effectiveness variables

	Time 1 (6 months prior to military discharge)	Time 2 (2 months prior to military discharge)	Time 3 (2 months post military discharge)	Time 4 (6 months post military discharge)
**Step 1: Reduce psychological pain (proximal)**				
**A. Reintegration difficulties & SDOH**				
Military to Civilian Questionnaire (M2C-Q; [54])	X	X	X	X
Employment and Education Status	X	X	X	X
Income and Savings	X	X	X	X
Brief Resilience Scale (BRS; [59]).	X			X
VA Homelessness Screening Clinical Reminder:	X			X
US DA Food Security	X			X
Criminal Behaviors	X			X
Well-Being Items^a^	X			X
Qualitative Questions^a^ (What motivated you to sign up for the sponsorship initiative?; What do/did you hope will come out of being involved with the sponsorship initiative? Thinking about your transition out of military service, what are/have been your top three concerns?)	X			X
**B. Health (proximal)**				
Depression; Patient Health Questionnaire-9 [38]	X	X	X	X
Generalize Anxiety Disorder (GAD-7 [61];.	X	X	X	X
PC-PTSD-5 [50]	X	X	X	X
The Alcohol Use Disorders Identification Test–Consumption (AUDIT-C) [8]	X	X	X	X
Level of Personality Functioning - Brief Form 2.0 [81]	X	X	X	X
Somatic Symptom Scale 8 (SSS-8)	X	X	X	X
VA Healthcare Enrollment/Utilization^b^	X	X	X	X
**Step 2: Promote connectedness (proximal)**				
The Social Support Survey (MOS SSS) [58]	X	X	X	X
Qualitative Questions^a^. Thinking about your experience with the sponsorship initiative, what about the program has been most beneficial for you? What things about the sponsorship program have you found least beneficial or could be improved? Would you recommend this program to another Servicemember or Veteran? Why or why not?				X
**Suicidal ideation and behaviors (distal)**				
Columbia-Suicide Severity Rating Scale [33]^a^	X			X

^a^Interview

^b^Assessed through VHA medical records

### Reintegration difficulties and social determinants of health

*Reintegration difficulties* will be broadly assessed using the Military to Civilian Questionnaire (M2C-Q; [54]), a 16-item measure that assesses difficulties in (a) interpersonal relationships with family, friends, and peers; (b) productivity at work, school, or home; (c) community participation; (d) self-care; (e) leisure; and (f) perceived meaning in life. The M2C-Q was initially validated in a sample of Iraq and Afghanistan Veterans seeking VA healthcare services [54] and has since shown strong construct validity and internal reliability in numerous Veteran samples [10, 53].

*Employment/education and income/savings status* will be assessed by asking TSMVs to self-report the income of themselves and (if applicable) their spouse/domestic partner and other immediate family members; current educational enrollment status; current work status; job satisfaction; hours worked/salary over the last week for themselves and (if applicable) their spouse/domestic partner; and money set aside for financial emergency. TSMVs who are not currently employed or enrolled in school will be asked to report whether they are actively looking for paid employment and strategies used to find paid employment. Those not actively looking for paid employment will be asked to provide reasons for not looking for paid employment.

We will also analyze broader societal impacts of TSMV employment and education using common job training benefit methodologies (e.g., [4, 42]). For example, we will calculate aggregate increases in productivity attributable to TSMV employment stemming from VSI participation, long-term growth in productivity associated with TSMV higher education pursuit, potential increases in tax revenue for municipalities, and reductions in social welfare benefit payments. To project these aggregate income, tax revenue, and social welfare benefit changes, we will use point estimates from the evaluation coupled with estimates on typical variation in productivity and social welfare benefits from labor market entry.

*Resilience* will be assessed using the Brief Resilience Scale (BRS; [59]), a six-item (e.g., “I tend to bounce back quickly after hard times.”) scale with strong evidence of validity, test-retest reliability, and internal consistency across samples [84].

*Homelessness* will be assessed using the VA Homelessness Screening Clinical Reminder (HSCR; [43]), a four-item (e.g., “In the past two months, have you been living in stable housing that you own, rent, or stay in as part of a household?”) measure that assesses current homelessness or imminent risk of homelessness among Veterans. The HSCR is considered standard care within VA settings to identify and respond to instances of Veteran homelessness.

*Food insecurity* will be assessed using the U.S. Adult Food Security Survey Module [70], a three-stage screening measure for assessing food insecurity. An example question is: “Within the past 12 months, the food that I bought just didn’t last, and I didn’t have money to get more.” A response of “often” or “sometimes” indicates food insecurity.

*Criminal behaviors* will be assessed using a series of self-report items, including “Within the last 12 months have you been issued a ticket of any kind for a traffic violation (e.g., speeding, failure to signal)?”; “Within the last 12 months have you been arrested or charged for any type of criminal offense (e.g., DUI, disorderly conduct, drug offense, domestic violence, assault, robbery)?”; and “Within the last 12 months, has a restraining order, no contact agreement, or order of protection been initiated or taken against you?” Many studies have suggested self-report methods show good agreement with official records and are a generally valid means of assessing criminal behavior (e.g., [45]).

*Well-Being Signs* is a three-item screening measure, based on the work of Vogt et al. [79] used to assess how TSMVs are doing in their daily lives. It asks TSMVs to rate what percentage of time (from 0 to 100%) that they have been “Fully satisfied with how things are going in these aspects of life?”, “Regularly involved in all aspects of life that are important to you?”, and “Functioning your best in aspects of life that you do participate in?”.

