### TSMV participants and recruitment

To participate in VSI, TSMVs must be at least 18 years old, approximately 6 months from military discharge, and planning to transition to one of the evaluation’s target cities during an active enrollment window (see Fig. 3). TSMVs will be recruited from military installations across the USA. The first 105 TSMVs enrolled per step will be assigned to the TAU condition, and the next 105 TSMVs per step will be assigned to the VSI.

The sample size was determined by completing a statistical power analysis using the powerlmm package [40] for R [52]. To test the primary hypothesis—that VSI reduces reintegration difficulties—using multilevel modeling with power of 80%, alpha of .05, and a small effect size (Cohen’s *d*=0.2). Total enrolled TSMVs needed across the six cities is 630. This sample size allows for adjustments required under randomization, design effects, and a dropout rate of 20% per follow-up.

Potential sponsors will be recruited in target cities using social media outreach with the local VA, Veteran service organizations, and college and university alumni networks. In accordance with previous research, we anticipate a sponsor attrition rate of approximately 20%. To mitigate the risk of a shortage of sponsors, the VSI aims to certify at least 600 sponsors across the evaluation.

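### The productivity, tax and welfare projections are described as built on the trial's point estimates, so the sampling error of the VSI effect is not carried into them and their uncertainty would be understated

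*Protocol article*

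**What the plan says.** In the Protocol article, the section Reintegration difficulties and social determinants of health adds a societal-impact analysis to the employment and education measures. Among its examples is: "we will calculate aggregate increases in productivity attributable to TSMV employment stemming from VSI participation". Long-term productivity growth from higher education, possible rises in municipal tax revenue and lower welfare payments are listed with it. The method is given in one sentence, for changes in aggregate income, tax revenue and welfare benefits: "we will use point estimates from the evaluation coupled with estimates on typical variation in productivity and social welfare benefits from labor market entry". The section also points to common job-training benefit methods, citing two sources.

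The trial was not sized for these outcomes. Under TSMV participants and recruitment, the primary hypothesis is "that VSI reduces reintegration difficulties", tested with "power of 80%, alpha of .05, and a small effect size". The resulting size is stated as: "Total enrolled TSMVs needed across the six cities is 630". Table 1 schedules employment and education status at all four time points.

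**The concern.** A projection of this kind has two uncertain inputs. One is the effect of VSI on employment or education, estimated from a few hundred people. The other is the external value placed on a person entering work or education. The sentence on method gives the first as a point estimate and attaches variation to the second only. An aggregate built that way treats the trial's estimate as if it were known.

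This matters because scaling an effect up to an aggregate scales its error by the same factor. If VSI had no effect on employment, an unbiased point estimate would still favour VSI about half the time, and a projection from it would then show a gain. Several of the listed outputs are also named in advance as increases or reductions, which leaves little room for a result whose sign is unclear.

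**Working it through.** **1. What the sections say, side by side.**
- Reintegration difficulties and social determinants of health: the trial input is point estimates, and the variation named concerns productivity and benefits on labour market entry.
- Analyses: multilevel models for the quantitative data, with no link from their standard errors to the projections.
- Sustainment: a budget impact analysis of implementation, intervention and VHA costs. It does not mention the productivity, tax or welfare projections.

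No section supplies the missing input.

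**2. What is dropped, in one formula.** Assume for illustration that an aggregate is proportional to Δ × v, where Δ is the VSI effect and v the external value. The article does not state this form. For independent inputs:

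Var(Δv) = Δ²·Var(v) + v²·Var(Δ) + Var(Δ)·Var(v).

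Holding Δ at its point estimate keeps the first term and drops the other two.

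**3. The plan's own figure.** The article gives no figure for the projections. The allocation adds up: "The first 105 TSMVs enrolled per step will be assigned to the TAU condition" and the next 105 to VSI, over three steps, so 105 × 2 × 3 = 630, or 315 per condition. The power basis behind 630 cannot be reproduced, because the intraclass correlation and slope variance are not given. Nothing here depends on it.

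**4. Numbers available at Time 4.**
- No loss: 315 per condition.
- A single 20% loss: 315 × 0.8 = 252.
- A 20% loss at each of three follow-ups (Times 2 to 4): 315 × 0.8³ = 315 × 0.512 = 161. That the loss compounds is my assumption; the article gives only a rate per follow-up.

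**5. Precision of an employment difference.** Assumptions: employment p of 50% to 70%, an unadjusted comparison of two proportions, no city or period design effect. The 95% half-width is 1.96 × √(2p(1−p)/n).

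| n per condition | p = 0.5 | p = 0.7 |
|---|---|---|
| 315 | 1.96 × √(0.50/315) = 0.078 | 1.96 × √(0.42/315) = 0.072 |
| 252 | 1.96 × √(0.50/252) = 0.087 | 1.96 × √(0.42/252) = 0.080 |
| 161 | 1.96 × √(0.50/161) = 0.109 | 1.96 × √(0.42/161) = 0.100 |

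**6. An illustrative 5-point gain.**
- 315 per condition: 5 ± 7.8 gives −2.8 to 12.8 points, and 5 ± 7.2 gives −2.2 to 12.2.
- 161 per condition: 5 ± 10.9 gives −5.9 to 15.9 points, and 5 ± 10.0 gives −5.0 to 15.0.

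Zero lies inside every interval. With v held fixed, the relative half-width of the aggregate equals that of Δ, here between 7.2/5 = 1.4 and 10.9/5 = 2.2 times the projected value.

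**The case against.** The best defence is that this is an ancillary analysis, described in a few sentences of a condensed article. Naming point estimates as base-case inputs is compatible with reporting intervals later. The text does not forbid intervals, and the cited job-training methods, which cannot be checked here, may deal with uncertainty. This has weight, and it limits the point to what the wording does. It does not remove the point, because the article does more than stay silent. It states which trial quantity enters the projection and which variation accompanies it, and the error of the VSI effect is in neither.

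The illustration is also open to challenge. The planned estimate would come from a multilevel model with covariates and all available data, not from an unadjusted comparison of Time 4 completers. Adjustment and repeated measures could narrow the interval; city and period effects could widen it. Employment rates and the 5-point gain are assumed, and education and income are inputs too. All of that stands, so the half-widths indicate an order of size and do not predict the trial's result.

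A reader might infer more than the article supports:
- That point estimates will be used exclusively. The article does not say so.
- That sampling error is the largest uncertainty. No figure is given for the external inputs, and extrapolating long-term productivity growth could contribute more.
- That these projections carry the funding case. The Sustainment section rests that on the budget impact analysis and on reports of implementation and effectiveness.
- That a non-significant difference will be presented as an attributable gain. The sentence on method uses the neutral word changes, and the tax item is called potential.

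**Conclusion.** The point holds as one about the stated method: as worded, the projections omit the sampling error of the VSI effect on employment or education, so their uncertainty would be understated. Under the assumptions in the working, the omitted 95% half-width is about 7 to 8 percentage points at full retention and about 10 to 11 points with compounded loss. Either is enough that a 5-point gain would not exclude zero.

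The consequence is limited. A linear projection from an unbiased estimate is not biased by lacking an interval; what goes wrong is the apparent precision. The primary hypothesis, the effectiveness models and the sample size are untouched. The documents do not support concluding that misleading gains will be reported. They support only that the described method does not guard against it.

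**What to change.** In the sentence on method, replace the point estimates with the adjusted VSI effect and its sampling distribution. Draw that effect by bootstrap or Monte Carlo together with the external productivity and benefit inputs. If a bootstrap is used, the resampling should respect the city structure of the model. Report every projected aggregate with its 95% interval, whatever its sign, and word each one as a change instead of a presumed increase or reduction.

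A rule that withholds a projection, or its attribution to VSI, whenever the interval includes zero is not needed. It would make significance a gate for an economic estimate, which is debatable; the interval already informs the reader.

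The cost is a short simulation step at analysis, with no new data and no change to design or sample size. The price is wider and less favourable headline figures.

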### Health and healthcare utilization

*Mental health difficulties* will be assessed using the Patient Health Quesitonnaire-9 [38], Generalized Anxiety Disorder Questionnaire [61], Primary Care PTSD 5 [50], Alcohol Use Disorders Identification Test–Consumption [8], and Level of Personality Functioning Scale-Brief Form 2.0 [81]. These brief measures have demonstrated strong validity and reliability across samples [1, 13, 15, 32, 38, 50].

*Somatic symptom* burden related to stomach problems, back pain, headaches, chest pain, dizziness, energy, and sleep will be assessed by the Somatic Symptom Scale 8 [26]. Previous studies with Veterans demonstrated good item characteristics and excellent reliability, a sound factor structure and significant associations with related constructs like depression, anxiety, pain, quality of life, and impairment [65].

*VA healthcare enrollment and utilization* will be assessed through data in access to the VA Corporate Data Warehouse (CDW), which enables evaluators to determine rates of VHA enrollment and utilization. Utilization outcomes will include the number of VHA encounters per TSMVs per year for in-person and video telehealth primary care, mental health, specialty care, and emergency department visits, as well as in-patient and acute hospital stays (e.g., acute medical/surgical or psychiatric inpatient care; [28]). Utilization of VHA-sponsored care in the community will be obtained from community care data (Patient Integrity Tool data and Fee Basis data).

### Social connectedness

Connectedness will be assessed using the Medical Outcomes Study Social Support Survey [58], a 19-item self-report measure of perceived availability of social support or connectedness that has demonstrated strong psychometric properties in military [20], Veteran [14, 66], and civilian samples [58].

### Suicide ideation and behaviors

Suicidal ideation and behaviors will be assessed using questions from the Columbia Suicide Severity Rating Scale screener [48] supplemented by questions based on cues provided in the full screener about suicide attempts and injuries [33].

### Qualitative data collection

#### Semi-structured interviews

TSMVs will also participate in qualitative interviews at Time 1 and Time 4 to facilitate formative evaluation. At Time 1, TSMVs will provide information about their motivation and hopes for VSI enrollment and primary concerns prior to military discharge. At Time 4, they will provide information about their experience with the VSI, including strengths of VSI and areas for improvement.

#### Periodic reflections

To identify event, adaptations, and contextual factors impacting adoption, implementation, and maintenance, the evaluators will also integrate periodic reflections—an innovative, low-burden method for documenting implementation phenomena such as barriers, facilitators, and adaptations that occur during implementation [21]. These lightly structured and guided reflections will occur monthly with members of the evaluation team and quarterly with other key partners (e.g., sponsors, CICs, military installations). These reflections will increase qualitative data points throughout implementation, thereby increasing the likelihood of identifying and understanding sources of variation in implementation.

